## Abstract

**Background:** Sepsis commonly causes acute respiratory distress syndrome (ARDS), and ARDS contributes to poor prognosis in sepsis patients. Early prediction of ARDS for sepsis patients remains a clinical challenge. This study aims to develop and validate chest computed tomography (CT) radiomic-based signatures for early prediction of ARDS and assessment of individual severity in sepsis patients. **Methods:** In this ambispective observational cohort study, a deep learning model, a sepsis-induced acute respiratory distress syndrome (SI-ARDS) prediction neural network, will be developed to extract radiomics features of chest CT from sepsis patients. The datasets will be collected from these retrospective and prospective cohorts, including 400 patients diagnosed with sepsis-3 definition during a period from 1 May 2015 to 30 May 2022. 160 patients of the retrospective cohort will be selected as a discovering group to reconstruct the model and 40 patients of the retrospective cohort will be selected as a testing group for internal validation. Additionally, 200 patients of the prospective cohort from two hospitals will be selected as a validating group for external validation. Data pertaining to chest CT, clinical information, immune-associated inflammatory indicators and follow-up will be collected. The primary outcome is to develop and validate the model, predicting in-hospital incidence of SI-ARDS. Finally, model performance will be evaluated using the area under the curve (AUC) of receiver operating characteristic (ROC), sensitivity and specificity, using internal and external validations. **Discussion:** Present studies reveal that early identification and classification of the SI-ARDS is essential to improve prognosis and disease management. Chest CT has been sought as a useful diagnostic tool to identify ARDS. However, when characteristic imaging findings were clearly presented, delays in diagnosis and treatment were impossible to avoid. In this ambispective cohort study, we hope to develop a novel model incorporating radiomic signatures and clinical signatures to provide an easy-to-use and individualized prediction of SI-ARDS occurrence and severe degree in patients at early stage.

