### 2.3. Sample Size Calculation

The sample size calculation based on logistic regression analysis approximately require 20 variables, regarded as risk factors for SI-ARDS, which are selected from radiomic features based on a previous study [20]. Meanwhile, the number of sepsis patients should be 5–10 times the number of risk factors. Considering a 25–50% occurrence rate of ARDS in sepsis patients [21,22], we calculate a minimum sample size of 160 patients for the discovering group.

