We intend to employ modified ResNeSt [24], DenseNet [25] and EfficientNet [26] models to train a robust model. All networks will use 3D convolution, ReLU/LeakyReLU nonlinear activation function and batch normalization. For the entire CT image and the outlined region of interest, we will train two convolutional neural networks to extract features. For the ROI, we will randomly sample the voxels containing 80% of the ROI from the entire CT image to generate an image. We will perform five-fold cross-validation on the training set in model training phase, and use random rotation, translation and transposition data enhancement strategies to increase the data and reduce the imbalance between classes. Additionally, the network will adopt the cross-entropy loss as a loss function, Xavier as initialized parameter and stochastic average gradient descent as optimizer. In the last fully connected layer of the network, we will modify the corresponding structure by adding pre-processed clinical variables and other data, and finally predicted whether ARDS might occur.

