### 2.7. Statistical Analysis

Continuous variables between two groups will be compared by T test or Wilcoxon rank sum test, whereas categorical variables will be compared by χ^2^ test. Univariate and multivariate logistic regression will predict occurrence of ARDS, using variables that selected by consensus of variable importance ranking by random forest [28] and least absolute shrinkage and selector operation (LASSO) regression techniques [29]. With the selected clinical and radiomics features, we will develop two versions of the ARDS prediction model, using logistic regression (LR) and support vector machine (SVM). Then a prognostic model will be built for prediction of individual and classification of severe level. ROC curves will determine the optimal cut-off point for models, and patients will be divided into high-risk and low-risk groups. VFD, RFFD and 28-day mortality will be screened indicators with LASSO-COX and RFE-SVM algorithm. Thereafter, these will be estimated using the Kaplan–Meier method. All these algorithm performances will be assessed using the AUC and *p*-values less than 0.05 will be considered statistically significant. After these main analyses, other subgroups will be carried out as following: septic shock vs. non-septic shock, and pulmonary sepsis vs. non-pulmonary sepsis. Statistical analysis will be performed using the R programming language, including its packages.

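### The named performance measures (AUC, sensitivity, specificity) cannot show whether individual ARDS risks are right, and the ROC cut-off is not tied to the development data

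*Protocol article*

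**What the plan says.** Section 2.7 (Statistical Analysis) names one measure: "All these algorithm performances will be assessed using the AUC". The Abstract gives a slightly longer list: "model performance will be evaluated using the area under the curve (AUC) of receiver operating characteristic (ROC), sensitivity and specificity, using internal and external validations". The article mentions no calibration plot, calibration intercept or slope, Brier score or recalibration step.

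The product is described in terms of the individual patient. The Abstract hopes for a model "to provide an easy-to-use and individualized prediction of SI-ARDS occurrence and severe degree in patients at early stage", the Discussion repeats that aim, and section 2.7 says "Then a prognostic model will be built for prediction of individual and classification of severe level".

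Two further statements bear on the point. In section 2.5, network training uses "data enhancement strategies to increase the data and reduce the imbalance between classes". In section 2.7, "ROC curves will determine the optimal cut-off point for models, and patients will be divided into high-risk and low-risk groups"; the dataset from which that cut-off comes is not named.

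**The concern.** AUC depends only on how patients are ranked. Any monotone distortion of the predicted risks leaves it unchanged, so a model can rank well while every probability it reports is wrong. Sensitivity and specificity at one threshold do not examine the probabilities either. The measures named therefore cannot support a claim of individualised prediction.

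The article itself gives three reasons why miscalibration is plausible:

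- There are few events per candidate variable, which tends to make predicted risks too extreme. The Discussion acknowledges possible overfitting.
- One of the two models is a support vector machine, whose native output is a score and not a probability.
- Augmentation is used partly to reduce class imbalance, and no later correction is stated.

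The cut-off raises a second issue. If the threshold is optimised on the same patients in whom sensitivity and specificity are reported, both are optimistic, and the published accuracy would not be reproduced at a fixed threshold.

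**Working it through.** **Inputs from the article.** About 20 candidate variables, 5–10 patients per variable, 25–50% ARDS and a discovering group of 160 (section 2.3); 40 testing and 200 validating patients (section 2.1). **Assumed, because the article does not give them:** a true AUC of 0.70–0.80, normally distributed scores with equal variance in the two classes, full 1:1 balancing as the limiting case, and a Youden-optimal cut-off.

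**1. The plan's own figure.** 20 × 5 = 100 and 20 × 10 = 200, so 160 lies within the stated rule (20 × 8 = 160), although the article does not fix the multiplier. In events, 160 × 0.25 = 40 and 160 × 0.50 = 80. Divided by 20 variables, that is 2 to 4 events per candidate variable.

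**2. Risk shift from class balancing.** Suppose a model is trained on classes balanced 1:1 from prevalence p and its output is not corrected. Then

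logit(predicted) = logit(true risk) + ln[(1 − p)/p].

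At p = 0.25 the added term is ln 3 = 1.10, so the odds are multiplied by 3. At p = 0.375 the multiplier is 0.625/0.375 = 1.67. At p = 0.50 it is 1.

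| True risk | Predicted, p = 25% | Predicted, p = 37.5% | Predicted, p = 50% |
|---|---|---|---|
| 10% | 25% | 15.6% | 10% |
| 25% | 50% | 35.7% | 25% |
| 50% | 75% | 62.5% | 50% |

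Averaged over patients, with class separation m = √2 × Φ⁻¹(AUC):

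- p = 25%: mean predicted risk is 0.470, 0.453 and 0.433 at AUC 0.70, 0.75 and 0.80. Divided by 0.25, expected/observed is 1.88, 1.81 and 1.73.
- p = 37.5%: mean predicted risk is 0.485, 0.476 and 0.466. Divided by 0.375, expected/observed is 1.29, 1.27 and 1.24.
- p = 50%: no shift.

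The shift is a constant on the logit scale, so the ranking and the AUC are the same in every case.

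**3. Optimism of a re-optimised cut-off.** In 5,000 simulated datasets per setting, the Youden-optimal cut-off was chosen and evaluated on the same patients, then compared with the true sensitivity and specificity at that cut-off. The ranges cover AUC 0.70–0.80 and ARDS rates of 25% and 50%.

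| Patients used to choose and evaluate | Apparent minus true (sensitivity + specificity) |
|---|---|
| 40 (testing) | 0.13–0.18 |
| 160 (discovering) | 0.06–0.09 |
| 200 (validating) | 0.05–0.07 |

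As an example, at AUC 0.80 and 25% ARDS the 40-patient set shows 0.802 + 0.769 = 1.571, while the chosen cut-offs truly deliver 0.665 + 0.742 = 1.407, an excess of about 0.16. With 200 patients the figures are 0.753 + 0.745 = 1.498 and 0.702 + 0.730 = 1.432, an excess of about 0.07. If the cut-off is frozen in the discovering group, the optimism in the testing and validating groups is about zero.

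**The case against.** The strongest reply is that a journal article condenses a fuller plan, and that calibration and the source of the cut-off may be specified there. Section 2.1 cites TRIPOD, though in connection with enrolment, the individualised aim is worded as a hope, and the Discussion says further validation is needed. This stands only in part. The article does not stay silent on performance. It names its measures, and section 2.7 applies AUC to all the algorithms. Those measures do not match the stated aim.

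A reader might infer that the predicted risks will be about double the truth. The documents do not support that. Section 2.5 sets no 1:1 ratio, near-doubling belongs to the corner of 25% ARDS with full balancing, and at 50% there is nothing to balance. Moreover, the imbalance statement concerns network training, whereas section 2.7 goes on to build a logistic regression and a support vector machine on selected features and states no rebalancing there. A logistic regression fitted to the patients as observed re-estimates its intercept and removes the average shift. The direct network output described at the end of section 2.5 could still carry it.

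A reader might also infer that the cut-off will be re-derived in each group. The article does not say so; it leaves the dataset open. The cut-off sentence comes straight after the model-building sentences, and the discovering, testing and validating groups are kept separate. Its stated use is to form risk groups, and the link to reported sensitivity and specificity comes through the Abstract. The optimism is therefore possible under the text, but not prescribed by it. In the external validation it would be modest, and the larger figure applies only to the 40 testing patients.

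**Conclusion.** The point holds as a mismatch between aim and measures. Followed as written, the evaluation could report a good AUC and could not show whether individual risks are correct, whatever the cause of any error. That conclusion does not depend on the rebalancing argument, since low events per variable and a non-probabilistic score are reason enough to check calibration.

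The sizes are conditional. An overstatement of 1.7–1.9 times needs 25% ARDS, full balancing and no recalibration. The cut-off inflation needs re-optimisation in the evaluated set and rests on the assumed AUC of 0.70–0.80. The remedy is inexpensive and should be adopted, but nothing here shows that the models will be miscalibrated or that the reported accuracy will be inflated.

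**What to change.** - In the 200 validating patients, report the calibration intercept, calibration slope, a calibration plot and the Brier score alongside AUC. In the 40 testing patients (40 × 0.25 = 10 to 40 × 0.50 = 20 events), report at most calibration-in-the-large and the Brier score, because a slope would be uninformative.
- If any model output comes from class-balanced training, re-estimate its intercept at the unbalanced ARDS rate of the development data before the model is frozen.
- State that the cut-off is derived once in the development data and frozen, and report sensitivity and specificity at that cut-off with confidence intervals.

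The cost is a few sentences and a few lines of analysis code, with no additional patients or data. Reported sensitivity and specificity may be slightly less favourable.

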## 3. Discussion

Mild ARDS patients, defined with OI ≤ 300 mmHg but >200 mmHg, may not require invasive mechanical ventilation, and the condition is more readily reversible [30]. To date, early lung-protective ventilation strategies with lower tidal volume ventilation that protect the lungs from the progression of injury, have revealed reduced mortality in ARDS patients [31,32]. Although SI-ARDS patients with end-stage refractory respiratory failure can be efficiently treated by venovenous extracorporeal membrane oxygenation (VV-ECMO), surviving patients with severe ARDS may progress to pulmonary fibrosis, resulting in a progressive decline of respiratory function and ending in death [33]. Thus, an early identification and classification of the SI-ARDS is essential to improve patients’ prognosis and disease management.

Until now, OI and radiologic features have been sought as classical indices to identify ARDS in sepsis patients. However, when OI declines and characteristic imaging findings are clearly presented, delays in diagnosis and treatment may be impossible to avoid. Two previous studies have tried to utilize the lung injury prediction score (LIPS) to predict risk for ARDS by collecting routinely available clinical data, but this LIPS model has a relatively low positive predictive value for ARDS and depends on a reliable portable chest radiograph interpretation [6,34]. Other multigene-based expression assays are also currently used to predict early SI-ARDS but their predictive utilities are still restricted in certain patient subsets who are characterized with the “reactive” phenotype [35,36,37].

Recently, artificial intelligence-based radiomics applied in predicting patients who are at risk of developing immunotherapy-induced pneumonitis and radiation pneumonitis have shown promising results [20,38]. Based on these findings, future studies could focus on comparing predictive values of different imaging approaches, such as CT, ultrasound and bronchoscopy combined with artificial intelligence technology. In this ambispective cohort study, we developed and validated a novel model incorporating radiomic signatures and clinical signatures to provide an easy-to-use and individualized prediction of SI-ARDS occurrence and severe degree in patients at early stage. Moreover, research has indicated that immune microenvironment abnormalities play a critical role in SI-ARDS [39,40], revealing that disturbances of neutrophil migration and neutrophil apoptosis caused neutrophil accumulation in the lung tissues, resulting in lung injury. We considered and initially explored correlation between radiomic features and immune-associated inflammatory indicators.

This study has several limitations. First, there are intrinsic limitations and possible patient selection bias in this observational and partly retrospective cohort study. Since the majority of sepsis patients first receive a chest X-ray, those with a relatively high risk of ARDS would be referred for chest CT and those with severe septic shock would receive bedside chest radiograph. However, a subgroup analysis will be performed by comparing mild sepsis group alone (removing the septic shock subgroup) with the pulmonary and non-pulmonary sepsis group. Second, the follow-up duration is relatively short. However, this period is quite adequate for consideration of the early primary outcome of SI-ARDS. A third limitation is the relatively small sample size and that high-dimensional extracted radiomics features may result in model overfitting. Therefore, these available data still remain inconclusive and need to be further validated in future multicenter prospective studies.

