Computerized tomography (CT) of the chest is easily accessible for patients in order for the identification of pulmonary or non-pulmonary sepsis and is also a method for ARDS diagnosis based on characteristic radiologic features. Also, radiomic high-dimensional features extracted from CT images offer an insight into microvascular injury of SI-ARDS, which are imperceptible to human eyes and relevant to intra-alveolar heterogeneity and potential prognosis. Herein, we used a single center ambispecive cohort study to develop a radiomics classification model and demonstrated the robust correlation between radiologic features and SI-ARDS occurrence. Further, we established a prediction model integrating radiomics and clinicopathological characteristics for more precise prediction of ARDS severity.

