### 2.4. Data Collection

All clinical data will be collected by investigators and trained personnel. Each participant’s data will be filled in electronic case report forms (CRF) and stored online using research electronic data capture (REDCap) [23]. The CRF is designed to collect the necessary information based on this study protocol. The detailed contents of CRF contain four main parts: (1) demographics and chronic disease history (including age, gender, smoking status, hypertension, diabetes mellitus, chronic lung disease and coronary heart disease), (2) laboratory tests and imaging examination (including routine blood, routine biochemistry, coagulation function, arterial blood gas analysis, blood culture, sputum culture, and ID of chest CT), (3) treatment process (including source of infection, anti-infection therapy, ventilator use or not, and type and dose of vasopressor therapy), (4) outcomes (intensive care unit (ICU) stay or not, length of ICU stay, total length of hospital stay, and in-hospital death).

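### The stated AUC analyses would not show what CT radiomics adds to routine clinical data, because no clinical-only benchmark or between-model difference is named

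*Protocol article*

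**What the plan says.** The Abstract sets the aim as "radiomic-based signatures for early prediction of ARDS and assessment of individual severity in sepsis patients". The Discussion explains the need: oxygenation index and imaging signs appear too late, and of the score built from routine clinical data it says that "this LIPS model has a relatively low positive predictive value for ARDS".

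The methods describe the occurrence model in two places, and both combine the two sources of information:

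- Section 2.5, on the last layer of the network: "we will modify the corresponding structure by adding pre-processed clinical variables and other data".
- Section 2.7, on the logistic regression and support vector machine: "With the selected clinical and radiomics features, we will develop two versions of the ARDS prediction model".

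On evaluation, section 2.7 says "All these algorithm performances will be assessed using the AUC" and gives a 0.05 significance level without a hypothesis. The Abstract adds sensitivity and specificity, with internal and external validation.

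The Introduction does speak of work to "develop a radiomics classification model and demonstrated the robust correlation between radiologic features and SI-ARDS occurrence", and then says "we established a prediction model integrating radiomics and clinicopathological characteristics for more precise prediction of ARDS severity". Sections 2.5 to 2.7 give the radiomics model no evaluation of its own. LIPS does not appear in the methods.

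**The concern.** The rationale is comparative: routine clinical information predicts ARDS too late or too poorly, and CT radiomics should do better. The planned measure is not comparative. The AUC of a combined model reflects everything that went into it, so a good value does not say whether the CT features or the clinical variables produced it.

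The clinical side may be strong. The case report form in section 2.4 includes "arterial blood gas analysis", from which PaO2/FiO2 can be derived when the inspired oxygen fraction is known. Section 2.6 grades ARDS by PaO2/FiO2. If such variables are selected into the model, part or much of its discrimination could come from them.

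At stake is the interpretation of the main result. A well-validated combined model could be reported as evidence for CT radiomics when the data had not been asked that question. Positive predictive value, the measure on which LIPS is criticised, is also not among the listed measures, so the reported results would not speak directly to that comparison either.

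**Working it through.** **No planned figure to reproduce.** The article states no target AUC, AUC difference or power. Its one sample size, 160 for the discovering group (section 2.3), rests on a patients-per-variable rule (160/20 = 8, inside the stated 5 to 10) and has no bearing on this comparison.

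**Inputs from the article.** 200 prospective validation patients (section 2.1) and an ARDS rate of 25–50% (section 2.3). This gives 200 × 0.25 = 50 to 200 × 0.50 = 100 cases.

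**Assumptions, not in the article.** Both models have AUC A = 0.78, and the correlation r between their AUC estimates is 0.3 to 0.8.

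**Step 1: standard error of one AUC (Hanley–McNeil).** With n1 cases and n0 non-cases:

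Var = [A(1−A) + (n1−1)(q1−A²) + (n0−1)(q2−A²)] / (n1·n0), where q1 = A/(2−A) and q2 = 2A²/(1+A).

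At A = 0.78: q1 = 0.6393, q2 = 0.6836, A² = 0.6084, A(1−A) = 0.1716.

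- 50/150: (0.1716 + 49 × 0.0309 + 149 × 0.0752)/7500 = 0.00172, SE 0.0415.
- 100/100: (0.1716 + 99 × 0.0309 + 99 × 0.0752)/10000 = 0.00107, SE 0.0327.

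**Step 2: 95% half-width of the paired difference** = 1.96 × SE × √(2(1−r)).

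| r | 50 cases | 100 cases |
|---|---|---|
| 0.3 | 0.096 | 0.076 |
| 0.5 | 0.081 | 0.064 |
| 0.7 | 0.063 | 0.050 |
| 0.8 | 0.051 | 0.041 |

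**Step 3: power for a true gain** (two-sided 0.05, assumed clinical-only AUC 0.70–0.75, r = 0.3–0.7). The SE of the difference comes from the two Hanley–McNeil variances and r; power = Φ(gain/SE − 1.96).

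| Gain | 50 cases | 100 cases |
|---|---|---|
| 0.05 | 16–34% | 22–50% |
| 0.10 | 50–89% | 69–98% |

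For example, with 50 cases, a clinical-only AUC of 0.70, a gain of 0.10 and r = 0.5, the SE is 0.043. Then Φ(0.10/0.043 − 1.96) gives about 64%.

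**Step 4: why the 40 internal test patients cannot carry the comparison.** Under the same assumptions, with 10 to 20 cases, power for a gain of 0.10 is only 14–43%. The prospective 200 are the place for it.

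**The case against.** Several points on the other side stand and limit the concern.

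- A reader might infer that AUC will be tested against 0.5. The article states no null value, and the 0.05 level may simply be a general one for all tests in section 2.7. If 0.5 were the null, significance in 200 patients would begin at about 0.59 (50 cases) or 0.58 (100 cases), but the article does not set that hypothesis.
- A reader might infer that radiomics is never modelled alone. The Introduction names a radiomics classification model, and in section 2.5 the image networks extract features before clinical variables join. What is missing is a stated evaluation of such a model; and it would not be a clinical-only benchmark in any case.
- A reader might infer that the study cannot show a contribution of CT. That is too strong. CT and clinical data come from the same patients, so the comparison remains open, and section 2.7 plans multivariable logistic regression. After selection by LASSO and random forest, that regression bears on adjusted association; it does not measure a gain in discrimination.
- The blood-gas route is plausible, not shown. Section 2.4 lists form contents, not predictors, and section 2.2 excludes patients with PaO2/FiO2 of 300 mmHg or less before admission, which narrows the range of that variable. Values above the threshold, or measured later, can still carry information.
- The stated product is a combined model, and validating it does answer that narrower aim.
- This is a condensed article, and a full plan may specify the comparison. However, the article does state its models and measures, and as stated these leave the motivating question open.

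**Conclusion.** The point holds in a limited form. The occurrence model described in the methods combines both sources and is judged by its own performance, so its AUC, sensitivity and specificity would not by themselves show what CT radiomics adds to routine clinical data. This is a worthwhile and inexpensive improvement to the stated analysis. It is not an internal contradiction, and it does not invalidate the combined model.

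How much of the combined AUC is clinical cannot be judged from the article, since the selected variables are unknown. Nor does the planned size guarantee a clear answer. Precision depends mainly on the number of ARDS cases and on the assumed correlation between models. The comparison can detect or exclude a gain of about 0.10 under reasonable conditions, but with 50 cases and low correlation even that is uncertain (power near 50%). A gain near 0.05 may well be left inconclusive. An interval for the increment is still more informative than no comparison.

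**What to change.** In section 2.7, add three models built with the same pipeline and frozen in the development data: clinical-only (including baseline PaO2/FiO2 if recorded), radiomics-only, and combined. In the 200 prospective patients, report each AUC and the paired difference, combined minus clinical-only, with its 95% CI. Base any claim of added value of CT on that interval, and say in advance that an interval covering both no gain and a useful gain will be reported as inconclusive. Where the LIPS items are on record, report that score alongside.

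The cost is a little more analysis on data already being collected, with no extra patients or procedures. The downside is that the headline may become a small or uncertain increment instead of a single AUC.
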